### 2.7. Study Size

According to Knofczynski and Mundfrom [53], to obtain (at least) a coefficient of determination (R^2^) of 0.5 with an excellent level of prediction using 3 independent variables, a total of 130 participants will be needed. Stratified probability sampling techniques will be used. Thus, the total number of participants will be divided into three strata following optimal allocation methods. A fixed cost has been assigned for each stratum (sedentary persons, C1; physically active subjects, C2; and athletes, C3, given that C3 > C2 > C1) to calculate the sample size of each population using Lagrange multipliers, given by the expression:(1)$$nh=n\;\frac{NhSh/\surd Ch}{\sum_{h=1}^{L}NhSh/\surd Ch},\;h=1,\;2,\;\ldots ,\;L$$
where, the values of *n_h_* correspond to the sample units for each stratum, *N_h_* is the maximum number of participants allowed, *C_h_* is the constant cost in all strata, *L* is the number of strata, and *S_h_* is the population quasi-variance of stratum *h*. The values obtained for the sedentary group are *n* = 54; for the physically active population group, *n* = 43; and for the athlete group, *n* = 33. To validate the new equation, the development/validation ratio will be 70/30 over the number of subjects participating in the study.

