### 2.8. Statistical Methods

The descriptive analysis of the anthropometric characteristics of the study population will be reported as means, standard deviations, and 95% confidence intervals. First, the total sample of participants will be used for the external validation of the RFM (to estimate whole-body-fat percentage) [26] and the Takai et al., equation (to estimate fat-free mass) [35]. A correlation analysis will be performed by calculating Pearson’s r, intraclass correlation coefficient (ICC), concordance correlation coefficient (ρ_c_), adjusted coefficient of determination (aR^2^), and root mean squared error (RMSE) as compared to DXA measurements. Smaller values of standard error of the estimate (SEE) and RMSE will indicate that the estimated values are closer to the DXA measurements. Bland–Altman diagrams will be used for the concordance analysis. This is a procedure to determine whether two measurement methods, X and Y, agree sufficiently to be declared interchangeable (D = X − Y). The mean of these differences represents the systematic error (bias), while the variance of these differences (1.96 SD) measures the dispersion of the random error.

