The development of the new equations to estimate fat mass (dependent variable) from different combinations of WG with sex, physical activity level, body mass, and stature (as predictor variables) will be carried out with multiple regression models under traditional (Ordinary Least Squares method) and Bayesian approaches (limited to three independent variables). For the latter, the ‘bayesbr’ and ‘bayes.lm’ R packages will be used. Variance inflation factors will be used to detect multicollinearity among predictors in the multiple linear regression models, and autocorrelation in the residuals will be assessed through the Durbin–Watson test. The variation explained by the model will be determined by the aR^2^. Finally, the SEE will be calculated for all generated models to measure the regression’s precision, while the RMSE will be used to evaluate how close the estimated values from each equation are to the actual measured values as reported elsewhere [42]. All possible regression models will be ranked using the akaike information criterion (AIC), the Bayesian information criterion (BIC), the Mallows’ C_p_, and the Hocking’s Sp. After compliance with all of the assumptions of the multiple regression analysis (normality of residual errors will be confirmed with the Omnibus k-squared and Jarque-Bera tests), the model with the better performance that includes WG will be selected for further analysis. The predictability of the equation in the selected model will be tested in the validation sample by calculating the aR^2^, RMSE, CCC, and ICC with its respective 95% CI. The concordance analysis will be performed by means of Bland–Altman diagrams, reporting the concordance intervals at 95%. Statistical tests will be carried out using the SPSS v26 statistical package (IBM Corp., Armonk, NY, USA) and the latest version of the environment for statistical computing R [54].

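### Agreement with DXA is summarised by one mean bias and one 1.96 SD band, so error that changes with level of fatness is counted as random and never quantified

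*Protocol article*

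**What the plan says.** Section 2.8 of the protocol article gives the purpose of the Bland–Altman analysis as deciding whether two methods "agree sufficiently to be declared interchangeable (D = X − Y"). It then defines the two parts of the error: the mean difference "represents the systematic error (bias), while the variance of these differences (1.96 SD) measures the dispersion of the random error". This definition appears with the external validation of RFM and of the athlete fat-free-mass equation.

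For the new equation, built with "multiple regression models under traditional (Ordinary Least Squares method) and Bayesian approaches (limited to three independent variables"), the section plans: "The concordance analysis will be performed by means of Bland–Altman diagrams, reporting the concordance intervals at 95" per cent. The other measures for that equation are "tested in the validation sample by calculating the aR^2^, RMSE, CCC, and ICC with its respective 95% CI". For the existing equations they are Pearson's r, ICC, the concordance correlation coefficient, adjusted R² and RMSE. Each is one number for the whole sample analysed.

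The section describes no regression of the difference on level, no calibration slope, no transformation and no limits by level or stratum.

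**The concern.** Under the stated definition, whatever is not the mean difference is random error. Error that depends on how fat the person is, and so is systematic for that person, goes into the 1.96 SD band. A near-zero mean bias can then support a claim of interchangeability while the equation over- or underestimates at one end of the range.

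The ends of the range are target groups here. The strata run from sedentary adults to athletes (2.3, 2.7). Section 1.1 quotes RFM obesity thresholds of 40% for women and 30% for men, and section 4 foresees use for individuals and in the national health system. RFM was derived in American adults and the fat-free-mass equation in male athletes (1.1), and section 3 says that such equations are specific to their populations. Miscalibration by level is therefore something that an external validation should be able to quantify.

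**Working it through.** **Inputs.** Sample size (2.7): 54 + 43 + 33 = 130; the 70/30 split gives 0.7 × 130 = 91 for development and 0.3 × 130 = 39 for validation. R² values: 0.5, the planning minimum (2.7: "to obtain (at least) a coefficient of determination (R^2^) of 0.5 with an excellent level of prediction using 3 independent variables"); 0.71, an earlier Colombian equation (1.1); 0.84, RFM (1.1). The SD of body-fat percentage implied by 1.1 is 3.51/√(1 − 0.84) = 8.78 from RFM and 7.04/√(1 − 0.36) = 8.80 from BMI. I use 8.8 points as an assumed scale; the new equation predicts fat mass, for which the article gives no SD.

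**1. What the single summary absorbs (any equation).** Let P be the predicted value, Y the DXA value, D = P − Y, and Y = a + bP + e. Calibration means a = 0 and b = 1.
- Mean difference = (1 − b)·mean(P) − a. This can be zero for any b, given a suitable a.
- Var(D) = (1 − b)²·Var(P) + Var(e). The miscalibration term enters the SD, and so the band that the plan calls random error.

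**2. What a calibrated least-squares equation shows.** Here Var(P) = Cov(P,Y) = R²·Var(Y). With M = (P + Y)/2:
- Cov(D,M) = −(1 − R²)·Var(Y)/2 and Var(M) = (1 + 3R²)·Var(Y)/4, so the slope of D on M is −2(1 − R²)/(1 + 3R²).
- The slope of D on Y is −(1 − R²). The slope of D on P is 0.
- The constant limits are ±1.96 × 8.8 × √(1 − R²).

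Decile means and coverage below come from a simulation of 2,000,000 draws with normal errors and constant variance. Overall bias is zero in every row.

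| R² | Slope on average | Slope on DXA | Slope on predicted | Mean error, outer DXA deciles | Constant limits | Coverage, outer DXA deciles | Coverage, outer predicted deciles |
|---|---|---|---|---|---|---|---|
| 0.50 | −0.40 | −0.50 | 0 | ±0.88 SD = ±7.7 | ±12.2 | 83% | 95% |
| 0.71 | −0.19 | −0.29 | 0 | ±0.51 SD = ±4.5 | ±9.3 | 88% | 95% |
| 0.84 | −0.09 | −0.16 | 0 | ±0.28 SD = ±2.5 | ±6.9 | 91% | 95% |

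The lowest DXA decile is overestimated and the highest underestimated. On the predicted axis, the only one a user of the equation has, bias is 0 and coverage nominal throughout. The predicted axis therefore separates miscalibration from compression towards the mean; the average axis does not.

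**3. Width of the limits.** With constant residual variance, the constant limits exceed limits drawn around the fitted line on the average axis by one factor at all levels: 1.12, 1.05 and 1.02 for the three R² values. Width that errs in opposite directions at the two ends needs residual spread that varies with level. In an assumed example (R² = 0.84, residual SD doubling from −2 to +2 SD of the predicted value), the correct half-width is 0.70 and 1.28 times the constant one in the lowest and highest predicted deciles, with coverage of 99% and 88%.

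**4. Precision with 39 people.** For a calibrated equation the standard error of the slope on P is about √[(1 − R²)/R²]/√39, that is 0.160, 0.102 and 0.070. The 95% CIs are about ±0.31, ±0.20 and ±0.14. In 5,000 simulated 91/39 splits with three predictors, the mean slope on P was 0.01 or less. The by-construction slope on the average reached p < 0.05 in 74%, 46% and 29% of runs.

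**The case against.** The strongest reply is that section 2.8 gives the ordinary Bland–Altman definition, never says that bias or limits hold at every level, and that a calibration slope is normal SAP detail. In part this stands: the article contains no contradiction, and an SAP not shown may add the slope. But the article itself fixes what counts as systematic and what as random, and ties this to interchangeability; that stated definition is what needs qualifying.

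Three stronger readings are tempting and not supported:
- A reader might infer that the limits will be too wide for lean and too narrow for fat participants. That needs heteroscedasticity, which is plausible for fat mass but not shown in the article.
- A reader might infer that a downward trend in the plot proves the new equation faulty. It does not, because calibrated predictions show the same trend.
- A reader might infer that the plan hides level-dependent error. The diagrams will be drawn and can display a slope or a fan; what is missing is a number for it.

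Two safeguards could be cited. The model is chosen only "After compliance with all of the assumptions of the multiple regression analysis (normality of residual errors will be confirmed with the Omnibus k-squared" and other tests); constant variance is one such assumption, although no check of it is named. That condition concerns developing the new equation. It does not cover the existing equations, and it does not test calibration in the validation sample. The concordance coefficient does penalise a difference in scale, but it pools this with scatter and bias. For a calibrated equation it equals 2R²/(1 + R²), that is 0.67, 0.83 and 0.91 at the three R² values, so a value below 1 does not identify miscalibration.

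**Conclusion.** The point holds in a limited form, as a cheap improvement to a stated method. As written, the plan would report level-dependent miscalibration of an equation as random error, and no planned statistic would reveal its size. The algebra in step 1 needs no distributional assumption.

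The point carries most weight for RFM and the athlete fat-free-mass equation. There the size and direction of any level-dependent error are unknown, so no magnitude can be given. The figures in step 2 apply only to a least-squares equation used in the population that produced it. They show compression towards the mean, not a defect, and they assume normal errors, constant variance and an SD of 8.8 points. R² of 0.5 is a planning floor; at the 0.84 quoted for RFM the slope on the average would be only −0.09.

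**What to change.** In section 2.8 or the SAP, for both validation analyses:
- Regress DXA on the predicted value and report the intercept and slope with 95% CIs (calibrated values 0 and 1). Regressing the difference on the predicted value is equivalent, with calibrated slope 0.
- Check whether the spread of the differences changes with the predicted value.
- Where bias or spread changes, report regression-based bias and 95% limits beside the overall ones, for example at the 10th, 50th and 90th percentiles of the predicted value.
- State that a slope against the Bland–Altman average is partly by construction, and do not read it alone as proportional bias.
- Base any statement on interchangeability on these results as well as on the overall mean and limits. Correct the wording that labels 1.96 SD a variance.

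The cost is one extra regression per comparison and a few more figures to report, from data already planned. With 39 validation participants the slope for the new equation will be imprecise, so judge it by its CI and not by a significance test.

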## 3. Expected Results

Diagnosing nutritional status generally involves the use of two indicators—body mass and stature—which, although necessary, cannot define body composition accurately. Currently, WG is used as a better predictor of cardiovascular risk and central obesity. Interestingly, scientific evidence supports the predictive potential of WG given the high correlation of WG-based equations with more reference methods (e.g., DXA and CT) for the assessment of body composition. However, these also have limitations that are mainly due to differences with respect to the population on which they have been developed since they are specific and, given the fluctuations that occur in age and sex, further external validation is warranted [40,55]. Development and validation of new models will increase generalizability and scientific soundness at the time of evaluating body composition in the Colombian population with different levels of physical activity. Thus, future research like this should take advantage of the predictive potential of WG together with other basic measurements (body mass and stature) to estimate with a low rate of error the fat mass and fat-free mass in different populations. Importantly, evaluating the performance of new models with different combinations of several variables (e.g., age, sex, body mass, stature, and WG) raises its relevance. Based on the available literature, we expect to find, after model specification, the body-mass-to-WG and WG-to-stature ratios as part of the best regression model. The body-mass-to-WG ratio has been previously found to have a strong correlation with body composition across the lifespan [56,57]. On the other hand, the WG-to-stature ratio has been reported as a better predictor of abdominal-fat distribution in men compared to BMI or the WG-to-hip ratio using computed tomography as a standard method [58]. In fact, some recent research suggests the WG-to-stature ratio is a strong predictor of abdominal obesity with no relevant age- or sex-dependent effects [59,60,61,62].

## 4. Conclusions

The importance of this study protocol (the F20 Project) is the validation of both existing and new models that might result in fewer estimation errors regarding body composition. This will contribute to the generation of public health alerts and strategies for promotion and prevention since the results obtained will provide more accurate diagnoses of nutritional statuses as compared to those currently in use (e.g., BMI). Hence, the results of the present project will be of great help in evaluating the nutritional status, at the individual and collective levels, of different populations in Colombia. Aware of the need for external validation, we expect to obtain an accessible and easy-to-apply tool in clinical nutrition, sports, and public health for the estimation of fat mass and fat-free mass. We consider that the simple, validated/developed equations might become formally established tools for use by the Colombian health system.

## Data Availability

Not applicable.
